
**Fig. 3 Fig3:**
[figure not shown]
Functional magnetic resonance imaging experiment paradigm (*REST* steady-state resting run; *TASK 1/2* block design bothersomeness and emotion stimulus run; *3D-T1W* structural image acquisition using 3-dimensional T1-weighted turbo field echo; *DTI* diffusion tensor imaging; *TASK 3* low-back-extension pain-model steady-state run)

**Table 1 Tab1:** The means and standard deviations (SDs) for valence and arousal of the groups to the International Affective Picture System (IAPS) items used in the study

	Negative emotion		Neutral emotion	
	Male	Female	Male	Female
Valence, mean (SD)	2.66 (0.40)	2.28 (0.54)	5.11 (0.27)	5.08 (0.34)
Arousal, mean (SD)	4.65 (0.60)	5.12 (0.71)	3.43 (0.56)	3.47 (0.61)
IAPS sequence number	2141, 2205, 2455, 2590, 2700, 2750, 2799, 2800, 3220, 3230, 3350, 6311, 6570, 9220, 9265, 9415		2038, 2102, 2191, 2215, 2220, 2235, 2357, 2383, 2393, 2396, 2397, 2410, 2445, 2487, 2495, 2499	

### fMRI and DTI data processing

The acquired fMRI and structural data will be processed with conventional analysis packages including FMRIB’s Software Library (FSL; http://fsl.fmrib.ox.ac.uk/fsl) AFNI (Analysis of Functional NeuroImages; https://afni.nimh.nih.gov/afni), and FreeSurfer (https://surfer.nmr.mgh.harvard.edu/) in data processing steps including physiological noise correction (3dretroicor, AFNI), head motion correction (mcflirt, FSL), skull stripping for fMRI data (BET, FSL) and structural data (mri_watershed, FreeSurfer), brain to brain registration (FLIRT and FNIRT, FSL) and statistical analysis.

### Outcome

#### Primary outcome measurement

The primary outcome measure is the bothersomeness of chronic sciatica as assessed by VAS [43]. To understand the impact of chronic sciatica on the patients, we decided to use the VAS for bothersomeness as the primary outcome measurement other than the VAS for pain intensity. Bothersomeness will be quantified using the VAS score as determined on a 100-mm horizontal line (0, no bothersomeness; 100, intolerable bothersomeness). Participants will be asked to mark the degree of bothersomeness due to sciatica experienced during the previous week at baseline (visit 2), before each treatment session (visits 2–9), and at each post-treatment follow-up visit (visits 10–11); the primary endpoint will be VAS for bothersomeness score at visit 10, i.e., 1 week after completion of the eight sessions of acupuncture treatment. The outcome measures will be assessed before treatment at each visit.

#### Secondary outcome measurements

VAS for pain intensity of chronic sciatica will be measured in the same fashion as VAS for bothersomeness (0, no pain; 100, intolerable pain) at baseline (visit 2), before each treatment session (visits 2–9), and at each post-treatment follow-up visit (visits 10–11). Since one of the goals of this study is to demonstrate the mechanism of acupuncture on chronic pain, we decided to use the VAS for pain intensity, for it is a fast and straightforward measure for assessing subjective intensity of pain [44].

The Oswestry Disability Index (ODI) [45] will be used to assess disability or dysfunction related to sciatica. The ODI consists of 10 questions on daily activities including: (1) experiencing general pain, (2) practicing self-care (e.g., washing, dressing), (3) lifting objects, (4) sitting, (5) standing, (6) walking, (7) sleeping, (8) travelling, (9) engaging in sexual activity if applicable, and (10) participating in social activities. Each item is rated on a 6-point scale (0–5), with lower scores indicating less pain-related disability. Participants will be asked to complete the validated Korean version of the ODI at baseline (visit 2) and at each post-treatment follow-up (visits 10–11).

The EuroQol 5-dimension (EQ-5D) [46] scale will be employed for health-related quality of life in patients with chronic sciatica. The EQ-5D consists of five dimensions including: (1) usual activities, (2) mobility, (3) pain/discomfort, (4) anxiety/depression, and (5) self-care. Each dimension is rated on a 1- to 3-point scale, with lower scores representing better health status. Participants will be asked to complete the validated Korean version of the EQ-5D at baseline (visit 2) and at each post-treatment follow-up (visits 10–11).

The Coping Strategies Questionnaire (CSQ) [47] will be used to evaluate the coping strategy for pain or acupuncture treatment. The CSQ is made up of 48 items across eight areas classified as either adaptive coping or maladaptive coping: (1) catastrophizing, (2) distractor behaviors, (3) self-instructions, (4) ignoring the pain, (5) reinterpreting the pain, (6) hoping, (7) faith and praying, and (8) cognitive distraction. Each item is rated on a 7-point Likert scale. The CSQ will be administered at baseline (visit 2) and at each post-treatment follow-up (visits 10–11).

The Korean version of Beck’s Depression Inventory (BDI) [48] will be used to measure depressive symptoms at baseline (visit 2) and at each post-treatment follow-up (visits 10–11). The BDI is a 21-item self-administered questionnaire with each item having a 0–3 point response format and a maximum theoretical score of 63. The psychometric quality of this test is very good [49].

The State-Trait Anxiety Inventory (STAI) [50] will be used to evaluate anxiety as a psychological factor at baseline (visit 2) and at each post-treatment follow-up (visits 10–11). The STAI consists of 40 items including: 20 items on the state of anxiety, which is triggered by a specific event and 20 items on the trait of anxiety, which is derived from personal characteristics. Each item is rated on a 4-point Likert scale, with lower scores indicating a lower degree of anxiety.

### Adverse events

Any expected or unexpected adverse events (AEs) will be recorded and described as frequency and percentage by the participants and practitioners at every visit until completion. Participants will be given notice of any cautions and possible AEs before the fMRI scanning and the acupuncture treatment. The AEs known as being related to acupuncture treatment include local bleeding or pain at the acupuncture points, local redness or bruising, and itching and dizziness during treatment [51]. If any serious AEs occur, detailed events including the date of occurrence, measures taken related to the treatment, causal relationship with the treatment, and treatment of the AEs will be announced immediately to the principal investigator and the Institutional Review Board (IRB) and direct actions will be supplied to those involved.

### Sample size

Referring to a previous study [52], an appropriately powered full-scale sample size was estimated using the mean difference of VAS for bothersomeness due to sciatica between groups in the primary endpoint. The researchers expect the mean difference will be 12.4 mm with a standard deviation (SD) of 16.2 mm between the two groups, which is not moderately clinically meaningful but represents a minimally important difference [53].

Considering the mean comparison method of the two-sample *t* test model with a two-tailed test, 80% test power, and a 5% significance level, the total number of individuals required per group is 27. For equal allocation of the two groups, the total sample size required when considering a dropout rate of 20% is 68 subjects with 34 subjects in each group.

Considering the nature of fMRI studies that use approximately 90,000 voxels to estimate the BOLD signal indirectly and for which conventional power calculations are meaningless, we determined 20 subjects in each group for fMRI scanning according to the trend of related neuroimaging studies [54–58]. Most studies decided that 20 participants is an adequate sample size regarding the high cost of fMRI examinations.

### Statistical analysis

All analyses will be performed using Statistical Package for Social Science (SPSS) for Windows (version 18.0; IBM Corp., Armonk, NY, USA) by a statistician blinded to the allocation of groups and the significance level will be set at 0.05. Statistical analyses will be conducted using the principle of the intention-to-treat (ITT) and the per-protocol (PP) analysis. We will apply the multiple imputation analysis for ITT analysis.

A paired *t* test (parametric) or Wilcoxon signed-rank test (non-parametric) will be used to compare continuous variables within groups. The two-sample *t* test (parametric) or the Mann-Whitney *U* test (non-parametric) for quantitative data and chi-square test or Fisher’s exact test for qualitative data will be performed to test differences between groups. Analysis of covariance (ANCOVA) will be used for adjustment of baseline characteristics if there is possibility of covariance. Repeated measure analysis of variance (ANOVA) will be performed for the different time point assessments between groups and interaction between groups and observed time. A mixed-model approach will also be used if necessary.

Statistical analysis for fMRI data will be completed via a general linear model (GLM) analysis (FEAT, FSL) and probabilistic independent component analysis (pICA using MELODIC, FSL). In performing GLM analysis, estimated responses from estimating regressors including stimulus function (block design) and nuisance regressors will be compared using a *t* test with the time series data in each brain voxel so that we can identify the specific brain responses to the visual and bothersome stimulus in TASK 1 and 2. pICA will be applied for fMRI data from REST and TASK 3 runs for brain functional connectivity analysis. In pICA processing, it assumes that the intrinsic sources in the data are non-Gaussian and the data can be inferred by Bayesian estimation of Gaussian noise. Then, the data can be projected in lower dimensional subspace and we can estimate the independent intrinsic component maps.

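### Adjustment for the baseline bothersomeness VAS is conditional on an undefined trigger; always fitting ANCOVA on that baseline would add precision at no cost and fix which test decides the trial

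*Protocol article*

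**What the plan says.** - **Endpoint.** Under Primary outcome measurement, "the primary endpoint will be VAS for bothersomeness score at visit 10". This is a final score, not a change from baseline.
- **Baseline.** The same section has patients rate bothersomeness "experienced during the previous week at baseline (visit 2), before each treatment session (visits 2–9"), so a pre-treatment value on the same scale exists for everyone.
- **Sample size.** "The researchers expect the mean difference will be 12.4 mm with a standard deviation (SD) of 16.2 mm between the two groups". The calculation uses a "two-sample *t* test model with a two-tailed test, 80% test power, and a 5% significance level", and "the total number of individuals required per group is 27". With 20% dropout this becomes 34 per group, 68 in all.
- **Analysis.** Under Statistical analysis, quantitative data are compared between groups by a two-sample t test or a Mann-Whitney U test. Then: "Analysis of covariance (ANCOVA) will be used for adjustment of baseline characteristics if there is possibility of covariance". Repeated-measures ANOVA is listed for the time course and the group-by-time interaction, and a mixed model is allowed where needed.
- **Analysis sets.** "Statistical analyses will be conducted using the principle of the intention-to-treat (ITT) and the per-protocol (PP) analysis". Multiple imputation is planned for the intention-to-treat analysis. Neither set is called primary.
- **Blinding.** The analysing statistician is blinded to allocation.

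**The concern.** In a trial of this size, the pre-treatment value of the outcome is usually the most useful covariate to hand. Adjusting for it lowers the residual variance by the square of its correlation with the outcome and costs one degree of freedom. Here it is collected, but its use hangs on a condition that cannot be applied as written: it does not say what counts as a possibility of covariance, who judges it, when, or for which variables.

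Two things are at stake:

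1. **Precision.** The target difference is, by the protocol's own account, only a minimally important one, and the planned power is 80% with little to spare.
2. **A fixed deciding test.** A t test, a Mann-Whitney test and an ANCOVA of the same visit-10 score can fall on different sides of 0.05, and the text does not say which one counts.

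**Working it through.** **Inputs from the Sample size section:** difference 12.4 mm, SD 16.2 mm (taken as the SD of the visit-10 score), two-sided 5%, 80% power, 20% dropout, 1:1 allocation. **Not in the document:** the correlation r between visit-2 and visit-10 VAS. It is an assumption, shown over a range.

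**Step 1. Reproduce the stated size** (normal approximation):

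n = 2 × (1.960 + 0.842)² × (16.2 / 12.4)² = 26.79, so 27 per group. Then 27 / 0.80 = 33.75, so 34 per group and 68 in total. The stated figures reproduce.

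**Step 2. Power of the unadjusted t test at 27 per group.** The noncentrality is 12.4 / (16.2 × √(2/27)) = 2.81. Power is 80.3% by normal approximation and 78.8% by the exact noncentral t (52 df). The exact method reaches 80% at 28 per group (80.3%).

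**Step 3. Power with ANCOVA on the visit-2 VAS, always fitted.** Residual SD = 16.2 × √(1 − r²), with 51 df:

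| Assumed r | Residual SD (mm) | Exact power, 27 per group | Gain over 78.8% (points) |
|---|---|---|---|
| 0.2 | 15.87 | 80.4% | 1.6 |
| 0.3 | 15.45 | 82.4% | 3.6 |
| 0.4 | 14.85 | 85.3% | 6.5 |
| 0.5 | 14.03 | 89.0% | 10.2 |
| 0.6 | 12.96 | 93.2% | 14.4 |

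The entry floor of 40 mm on this VAS narrows the baseline range and may lower r, so the upper rows should not be taken for granted.

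**Step 4. Error rate under the null**, simulated with 27 per group and normal data:

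- *Each test used alone* (20,000 runs): 4.7 to 4.9%.
- *Smallest p-value of t, Mann-Whitney and ANCOVA* (20,000 runs): 6.9% at r = 0.3 and 8.1% at r = 0.5. It rises to 8.8% at an r of 0.7.
- *ANCOVA only if baseline differs at p < 0.05, otherwise the t test* (20,000 runs): 4.7%, 4.3% and 3.6% at r = 0.3, 0.5 and 0.7.
- *Shapiro-Wilk choice between t and Mann-Whitney, with ANCOVA when baseline differs at p < 0.05, or when it correlates with outcome at p < 0.05* (10,000 runs, r = 0.3 to 0.6): about 4 to 5%.

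Free choice of the best result inflates the error rate. A trigger set in advance, of the kind the wording most plausibly intends, does not.

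**The case against.** **The unadjusted test is valid.** A two-sample t test in a 1:1 randomised trial is unbiased, matches the test used for sizing, and delivers the planned power by the method used. This stands: the point is lost efficiency, not invalidity. The gain depends on a correlation that the document does not give, and at r = 0.2 it is under 2 points.

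**The t test is the natural default.** The endpoint is fixed at one visit, the sample size rests on the t test, and that test comes first among the between-group methods. A reader might infer that all the listed tests have equal standing, or that adjustment waits until an imbalance is seen. The text says neither. Still, the default has to be inferred, and the conditional sentence can displace it.

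**The 5% level is not shown to be broken.** A reader might infer that choosing the test from the data inflates the error rate as planned. The documents do not support that: no rule of reporting the smallest p-value is written, and plausible pre-set triggers hold about 5% or less. A much larger inflation might be inferred by also counting the repeated-measures tests and the per-protocol versions. That is not supported either, because the repeated-measures ANOVA addresses the time course rather than the visit-10 difference, and any such figure needs a correlation structure that the document does not give.

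**Blinding.** A statistician blinded to allocation is less able to choose in a favoured direction. This helps, but a p-value is visible under masked group labels, so it does not fix the test.

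**The detail may sit in an analysis plan.** Model details often do. Here, however, the article is not silent: it states a conditional rule, and a plan that always adjusted would have to depart from it.

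**Conclusion.** The point holds as a free improvement and a rule that needs tightening, not as an error that invalidates the trial. The stated sample size is consistent with its inputs. By leaving baseline adjustment conditional, the plan gives up between about 2 and 14 percentage points of power at 27 completers per arm, for assumed correlations from 0.2 to 0.6. The size of the gain rests on that correlation, on 16.2 mm being the SD of the visit-10 score, and on approximate normality.

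The undefined trigger also leaves the deciding test open. About 7 to 8% (r = 0.3 to 0.5) is an upper bound on the false-positive rate under free selection among three tests, and not the expected rate of the plan as written.

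**What to change.** For the primary outcome, delete the conditional clause and state one primary analysis: ANCOVA of visit-10 bothersomeness VAS on treatment arm and visit-2 VAS, always fitted, in the intention-to-treat set, with the treatment coefficient and its 95% confidence interval pooled over the multiple imputations. A regression coefficient with its standard error pools directly; a Mann-Whitney p-value does not.

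Label the t test, Mann-Whitney, repeated-measures ANOVA, mixed-model and per-protocol results as supportive, so that none can replace the primary result. The sample size can stay as it is, and the extra precision serves as a margin.

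The cost is about two sentences, with no new data, patients or software. The change should be dated and made before unblinding.

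### The firm longitudinal analysis is repeated-measures ANOVA, with a mixed model only on an unstated trigger; the mixed model should be the standing method (minor, primary test unaffected)

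*Protocol article*

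**What the plan says.** All of this stands in the protocol article.

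- **Schedule (Primary outcome measurement).** The bothersomeness VAS is recorded at baseline (visit 2), "before each treatment session (visits 2–9), and at each post-treatment follow-up visit (visits 10–11"). Visit 2 serves as baseline, so there are 8 + 2 = 10 ratings. Each covers the previous week and is taken before treatment.
- **Primary endpoint (same section).** It is one time point: "the primary endpoint will be VAS for bothersomeness score at visit 10".
- **Sample size.** The trial is powered on a two-sample t test: "the mean difference will be 12.4 mm with a standard deviation (SD) of 16.2 mm between the two groups", giving 27 per group, or 34 per group (68 in total) after 20% dropout.
- **Between-group tests (Statistical analysis).** "The two-sample *t* test (parametric) or the Mann-Whitney *U* test (non-parametric) for quantitative data" come first, followed by a conditional adjustment: "Analysis of covariance (ANCOVA) will be used for adjustment of baseline characteristics if there is possibility of covariance".
- **Longitudinal analysis (same section).** "Repeated measure analysis of variance (ANOVA) will be performed for the different time point assessments between groups and interaction between groups and observed time". Then: "A mixed-model approach will also be used if necessary". No trigger for the mixed model and no sphericity correction are given.
- **Missing data (same section).** "We will apply the multiple imputation analysis for ITT analysis". The per-protocol analysis has no corresponding statement.

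**The concern.** The firm commitment is to the weaker method, and the better one depends on a judgement that could be made after seeing data.

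Three properties of repeated-measures ANOVA matter here. First, its within-patient tests, including group-by-time, assume sphericity. Ten ratings a few days apart, with one-week recall windows that overlap between twice-weekly sessions, are likely to correlate more strongly when close in time, which breaks that assumption. Second, if visit 2 is a level of the time factor, the group main effect averages in a time at which no treatment effect can exist. That main effect is not the visit-10 difference that the trial was designed to detect. Third, the method needs complete rows wherever data are not imputed.

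At stake is the reading of the longitudinal results. They could appear to contradict the visit-10 comparison, or show a group-by-time interaction, for technical reasons alone.

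**Working it through.** **1. The plan's own figure.** With a difference of 12.4 mm, SD 16.2 mm, two-sided 5% and 80% power: n = 2 × [16.2 × (1.960 + 0.842) / 12.4]² = 26.79, so 27 per group. Then 27 / 0.80 = 33.75, so 34 per group and 68 in total. The stated figures reproduce. Exact noncentral-t power at 27 per group is 78.8%.

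**2. Assumptions.** The documents give neither the correlation between ratings nor the time course of the effect. I take 27 per arm, full data and SD 16.2 mm at every visit. The correlation is compound symmetry (CS) 0.3 to 0.7, first-order autoregressive (AR) 0.7 to 0.9 per visit, or a mixture, 0.3 + 0.7 × 0.8^lag. Visit 2 is counted as a level of the time factor.

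**3. What the group main effect estimates.**
- Linear build-up to visit 10, held at visit 11: [12.4 × (0 + 1 + … + 8)/8 + 12.4] / 10 = (55.8 + 12.4)/10 = 6.82 mm.
- The same, halved at visit 11: (55.8 + 6.2)/10 = 6.2 mm.
- Full effect from visit 3: 9 × 12.4 / 10 = 11.16 mm.

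**4. Power formulas.** The SD of a patient's ten-rating mean is 16.2 × √(average entry of the correlation matrix). Under CS 0.5 this is 16.2 × √0.55 = 12.01 mm. The noncentrality for the linear pattern is then 6.82 / (12.01 × √(2/27)) = 2.09, giving 53.5% power on 52 df. For the baseline-adjusted visit-10 comparison the SD is 16.2 × √(1 − ρ²), where ρ is the correlation between visits 2 and 10. Under CS 0.5 this is 14.03 mm, giving 89% on 51 df. The interaction columns come from 4,000 simulated trials per setting.

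| Correlation | Main effect, linear | Main effect, full from visit 3 | Visit 10, baseline-adjusted | Interaction type I error, uncorrected | Same, Greenhouse-Geisser |
|---|---|---|---|---|---|
| CS 0.3 | 70% | 98% | 82% | 5.3% | 4.2% |
| CS 0.5 | 54% | 92% | 89% | 4.6% | 3.8% |
| CS 0.7 | 43% | 83% | 97% | 4.8% | 3.6% |
| AR 0.7 | 65% | 97% | 79% | 9.5% | 4.5% |
| AR 0.8 | 54% | 92% | 80% | 11.2% | 4.5% |
| AR 0.9 | 43% | 83% | 86% | 11.5% | 4.7% |
| Mixture | 45% | 85% | 86% | 10.4% | 4.8% |

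If the effect halves at visit 11, main-effect power under CS and AR falls to 37–62%. Under the linear pattern the Greenhouse-Geisser interaction test has 46–98% power, so it is not uniformly weak.

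**5. Missed ratings, only where data are not imputed.** With 20% dropout and an assumed 2% chance of missing each of the nine post-baseline ratings, 0.80 × 0.98⁹ = 66.7% of patients have all ten, or 34 × 0.667 = 22.7 per arm. Visit 10 alone would have 34 × 0.80 × 0.98 = 26.7. At 1%, 3% and 5% the complete-case numbers are 24.8, 20.7 and 17.1 per arm.

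**The case against.** The strongest reply is that this is a supportive analysis. The primary endpoint is the visit-10 score, the sample size rests on a two-sample t test, and that test is listed first for between-group differences. Nothing says that repeated-measures ANOVA decides the trial. That stands. A reader might infer that the primary result is diluted or the trial under-sized, and the documents support neither.

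A reader might also infer that the ANOVA discards every patient with a missed rating and so breaches ITT. The same section plans multiple imputation for ITT, so listwise loss concerns only per-protocol or unimputed analyses. Nor does imputation leave nothing to pool: with two arms the group effect is one mean difference, and multi-parameter tests can be combined across imputed sets.

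Sphericity does not touch the between-group main effect, and naming a correction is commonly left to an analysis plan. That also stands. So does the point that treating visit 2 as a time level is an inference. The ANOVA sentence is not tied to the VAS either; ODI, EQ-5D, CSQ, BDI and STAI have only three time points. Finally, the loss of power depends on the trajectory: with early onset the main effect often matches or beats the visit-10 comparison.

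The order of commitment survives all of this. The article itself fixes the ANOVA as firm and the mixed model as conditional with no trigger. Full data, or perfect imputation, removes neither the sphericity problem nor the difference in estimand.

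**Conclusion.** The concern holds as a minor point about the longitudinal analysis. The uncorrected group-by-time test rejects about 10–11% of the time under serially decaying correlation (9.5–11.5% over the settings tried) and about 5% under compound symmetry. The group main effect, if visit 2 is a time level, averages 12.4 mm down to 6.2–6.8 mm under gradual onset, but only to 11.2 mm under early onset. Across all the correlations tried, gradual onset held to visit 11 leaves it weaker than the baseline-adjusted visit-10 comparison; early onset does not do so consistently.

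These sizes rest on assumed correlations and trajectories. No change to the sample size or to the visit-10 primary comparison follows, and the ITT analysis does not become a complete-case analysis.

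**What to change.** In Statistical analysis, replace the ANOVA and mixed-model sentences with an unconditional commitment. The longitudinal analysis of the VAS is a likelihood-based mixed model for repeated measures with these terms:

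- Outcome: post-baseline VAS at visits 3 to 11.
- Fixed effects: arm, visit, arm-by-visit, visit-2 VAS and visit-2 VAS-by-visit.
- Covariance: unstructured.
- Patients: all randomised patients with any post-baseline rating.
- Report: the arm contrasts at visit 10 and visit 11.

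Drop repeated-measures ANOVA, or label it supportive and state the sphericity correction.

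The cost is wording only, since the plan already names a mixed model. One small downside is that an unstructured covariance over nine visits has 9 × 10 / 2 = 45 parameters for 68 patients, so a simpler fallback structure should be stated in advance.

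There is no need to thin the ratings to visits 4, 6, 8, 10 and 11 to avoid overlapping recall. They are not all a week apart: visit 9 is 3 to 4 days after visit 8 and visit 10 is a week after treatment ends, so visits 8 and 10 are about 10–11 days apart. The text does not date visit 11. The covariance already accommodates the overlap.
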